### Sample size calculation

Based on our pilot data, we anticipate the incidence of the primary composite outcome to be 35 % pre-EASE (cohorts (i) and (iii)) [55–57]. A 10 % absolute difference in the primary endpoint is considered to be the minimal clinically important difference to detect (a commonly used threshold for many interventions [58]). Accordingly, assuming an alpha = 0.05, beta = 0.2 (80 % power), a 15 % decline in the primary outcome post-EASE, a 5 % decline in the primary outcome in the control group (10 % absolute overall ‘difference of differences', 1:1 recruitment of cases to controls), we will require 140 patients per centre (UAH, Edmonton and FMC, Calgary) or 280 patients total. Since all enrolled patients will be followed by chart review to ascertain the primary outcome, there will be no drop-outs and no sample size adjustment will be required for attrition. However, a priori, we have decided to double the required sample size (280 patients per site or 560 in total) to account for the likelihood of high attrition at follow up. Given the absence of previous studies, after collecting data on the first 140 patients (total of both sites), we will calculate an updated sample size calculation.

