**Methods/design:**

Prospective, before-after study with a concurrent control group. Four cohorts of 140 consecutively-screened older patients (≥65 years old) will be enrolled (560 patients in total). The EASE interventions involves co-locating all older surgical patients on a single unit, involving an interdisciplinary care team (including a geriatric specialist) in the development of individual care plans, implementing evidence-informed elder-friendly practices, use of a reconditioning program, and optimizing discharge planning. Subjects will be followed via chart review for their hospital stay, and will then complete in-person or telephone interviews at 6 weeks and 6 months after discharge. Measured outcomes include clinical (postoperative major in-hospital complication or death [primary composite outcome]; death or readmission within 30-days of initial discharge; length of hospital stay), humanistic (quality of life; functional, cognitive, and nutritional status) and economic (health care resource utilization and costs) endpoints. Within-site mean change scores will be computed for the composite primary outcome and the overall covariate-adjusted between-site pre-post difference will be the dependent variable analyzed using generalized linear mixed model procedures including adjustment for clustering.

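### The stated 280 patients do not give 80% power for the 10-point difference of differences; power is about 15% at 280 and about 26% at the full 560

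*Protocol article*

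**What the plan says.** The abstract's Methods/design paragraph describes the design as "Four cohorts of 140 consecutively-screened older patients", 560 patients in all. Study design sets these out as two sites by two periods, with different patients in each cohort. Data analysis makes the between-site difference in pre-post change the primary analysis, using a mixed model with adjustment for site and operating surgeon.

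Sample size calculation takes a pre-EASE event rate of 35% at both sites, alpha 0.05, 80% power, "a 15 % decline in the primary outcome post-EASE" and a 5% decline in controls. It describes the target as a 10% absolute difference of differences, which is also its minimal important difference. From these inputs it concludes that "we will require 140 patients per centre (UAH, Edmonton and FMC, Calgary) or 280 patients total".

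It then says that the primary outcome will have no drop-outs, but that "we have decided to double the required sample size" because of expected attrition at follow-up, which gives 280 per site. Finally, "after collecting data on the first 140 patients (total of both sites), we will calculate an updated sample size calculation".

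**The concern.** A difference of differences is estimated from four independent proportions, and each adds its own sampling variance. A two-group calculation has only two such terms. A required size of 140 per centre, or 70 per site and period, looks far too small for a 10-point contrast of this kind with event rates between 20% and 35%.

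The primary endpoint's power claim is at stake. As written, a reader will believe that 280 patients give 80% power for the effect the plan calls minimally important, and that 560 give more. If the true figure is about a quarter, the study would miss an effect of exactly that size roughly three times in four.

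**Working it through.** **Inputs, all from Sample size calculation unless noted**
- Event rates: 0.35 pre and 0.20 post at the intervention site; 0.35 pre and 0.30 post at the control site. The declines are read as absolute, because the section calls their difference absolute.
- Target contrast: (0.35 − 0.20) − (0.35 − 0.30) = 0.10.
- Alpha 0.05, power 80%. Sidedness is not stated; two-sided is assumed (z = 1.96 and 0.8416) and one-sided is also shown.
- Patients per cohort: 280/4 = 70 for the stated requirement; 560/4 = 140 for the enrolled number (Study design).

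**Step 1: reproduce 140**

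The pooled two-group formula is n = [1.96·√(2p̄(1−p̄)) + 0.8416·√(p₁(1−p₁) + p₂(1−p₂))]² / (p₁−p₂)².
- 15% vs 5%, with the two declines treated as if they were event proportions: [1.96·√0.18 + 0.8416·√0.175]² / 0.01 = 140.1 per group.
- 35% vs 20%, the intervention site's pre-post change alone: [1.96·√0.39875 + 0.8416·√0.3875]² / 0.0225 = 137.9, so 138 per group.
- 30% vs 20% gives 294 per group and 35% vs 25% gives 329, so neither matches.

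Two ordinary two-group calculations therefore land on or very near 140.

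**Step 2: variance of the contrast actually planned**

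With n per cohort, Var = [0.35·0.65 + 0.20·0.80 + 0.35·0.65 + 0.30·0.70]/n = (0.2275 + 0.16 + 0.2275 + 0.21)/n = 0.825/n.

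**Step 3: power at the stated sizes, Φ(0.10/SE − 1.96)**

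| Total | Per cohort | SE | 0.10/SE | Power | Simulated |
|---|---|---|---|---|---|
| 280 | 70 | 0.1086 | 0.921 | 14.9% | 15.6% |
| 560 | 140 | 0.0768 | 1.303 | 25.5% | 25.9% |

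**Step 4: precision and detectable effect at 140 per cohort**
- 95% CI half-width: 1.96 × 0.0768 = 0.150, or about 15 points.
- Effect detectable with 80% power: (1.96 + 0.8416) × 0.0768 = 0.215, or about 21.5 points.

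**Step 5: size that corresponds to 80% power for 10 points**

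n = (1.96 + 0.8416)² × 0.825 / 0.10² = 647.5, so about 648 per cohort or 4 × 648 = 2,592 in total. That is 2,592/560 ≈ 4.6 times the enrolled number.

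**Step 6: sensitivity at 560**
- One-sided alpha 0.05: power 37%.
- Logit scale: interaction −0.539, SE 0.376, power 30%.
- Variance computed with all four rates at 35% (sum 0.91): power 24%.
- Reading 140 per centre as 140 per centre and period gives the same 560 patients and the same 26%.

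**The case against.** **Covariate adjustment.** The primary model adjusts for many baseline variables, which could sharpen the contrast. Reaching 80% power at 140 per cohort would need the variance cut by 1 − 140/647.5 = 78%. Halving the variance is equivalent to 280 per cohort and gives 45%. The surgeon clustering named in Data analysis is not allowed for in the sample size and would normally work in the other direction. This objection does not rescue the figure.

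**The planned update.** The recalculation after 140 patients is a real opportunity for correction, and the article does not give its formula, so one cannot say it would repeat the problem. It still does not correct the printed figure. By the recruitment schedule in Study design and Discussion, 280 pre-EASE patients are enrolled before implementation. The first 140 should therefore all be pre-EASE and can inform only the baseline rate. That is an inference from the schedule and is not stated in the sample size section.

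**Stronger readings that the document does not support.**
- A reader might infer that 140 came from 35% vs 20% and that the control-site change was left out. The 15% vs 5% calculation fits at least as well: it uses both declines, gives the 10-point difference and attaches naturally to a number per centre. If that was the route, the control-site change was used, and the fault lies in treating each site's change as a single binomial proportion. The origin is unproven.
- A reader might infer that the doubling was offered as reserve power for the primary outcome. The article justifies it by attrition at follow-up and says that the primary outcome has no drop-outs. The doubling is at fault only in that its base, 280, is not the requirement for the primary contrast.

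**Conclusion.** The concern holds: the stated sample size does not follow from the plan's own inputs and primary contrast. Power for the 10-point difference of differences is about 15% at 280 patients and about 26% at 560, against the stated 80%; no variant tried at 560 exceeds 37%. An observed 10-point reduction at 560 would carry a 95% interval of roughly −25 to +5 points and would not be significant.

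This rests on four independent cohorts, absolute declines, the stated event rates, a normal approximation and no clustering. It does not depend on how 140 was obtained. Because this is a stated figure that contradicts its own inputs, it cannot be left for an analysis plan to fill in.

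**What to change.** In Sample size calculation:
1. Replace the power statement with: *140 patients per cohort give about 26% power for a 10-point difference of differences, 80% power for about 21.5 points, and an expected 95% confidence interval half-width of about 15 points.* Note that this makes no allowance for surgeon clustering.
2. Delete the claim that 280 patients suffice for 80% power, and the description of 560 as double the requirement as far as the primary outcome is concerned. The follow-up attrition rationale can stay for the interview outcomes.
3. State that the update after the first 140 patients will use the four-cohort variance and, since those patients are expected to be pre-EASE, that it informs the baseline rate only.

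The cost is a change of wording. No extra patients are needed, and power stays near 26%. The stated power becomes less favourable, but it then matches the planned analysis.

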### Ethical and other considerations

The EASE study protocol has received approval from the University of Alberta Research Ethics Board (Pro00047180) and the University of Calgary Conjoint Research Ethics Board (REB140729). The trial has received peer reviewed funding from Alberta Innovates Health Solutions (grant # 201300465) and has been formally registered at clinicaltrials.gov (NCT02233153).

An exemption from patient consent at baseline (in-hospital stay via chart review) has been granted, as patients will be acutely ill and will require sedatives and pain killers making obtaining informed consent at that stage impossible. Signed informed consent will be obtained prior to hospital discharge so that in-person and telephone follow-up interviews can be performed, 6 weeks and 6 months post discharge.

## Discussion

In summary, EASE is a prospective, before-after study with a concurrent control group. EASE aims to assess the impact of an elder-friendly surgical unit with the goal of delivering evidence-informed care to improve the quality of care to older acute surgical patients and result in optimal use of health care resources.

Given the current aging population and the rising burden of chronic disease and frailty, new patient-centred, comprehensive and interdisciplinary models of Acute Care Surgery are needed to optimize care in this vulnerable patient population. This proposed research will generate new knowledge on acute surgical outcomes in older patients and validate the novel model of care, including assessment of the associated economic benefits. If effective, we expect the EASE initiatives to be generalizable to other surgical centers.

EASE commenced enrolment in April 2014. Recruitment of all pre-EASE subjects is expected by spring 2015, with implementation of the EASE initiatives in summer 2015. Completion of all post-EASE subject recruitment is expected to take until mid-2016, with final study results anticipated in late 2016.

## Abbreviations

ACS: Acute care surgery
EASE: Elder-friendly approaches to the surgical environment
HRQL: Health-related quality of life
QALY: Quality adjusted life year
